### Pharmaceutical intervention

Participants allocated to the pharmacotherapy group will be prescribed trazodone as a regular treatment for the study duration. Participants will be initially instructed to meet with the psychiatrist on the research team through video sessions. The psychiatrist will provide information on trazodone usage, possible side effects, and drug interactions. All participants in the pharmacotherapy group will receive a starting dose of 50mg/day at their first session and are encouraged to contact the psychiatrist’s office if they experience any side effects or have concerns about the medication. The psychiatrist will get back to them via phone on the same day and discuss potential dosage adjustments according to the participants’ circumstances. Additionally, a psychiatrist will follow up with the participant mid-program (week 4) via video sessions. During these follow-up appointments, dosage may be adjusted according to drug effectiveness and possible adverse effects. The maximum dosage for trazodone is 100mg/day for this study. These low doses (50mg-100mg) enable trazodone to produce hypnotic effects without causing tolerance or daytime drowsiness [11]. Participants will continue to take their medication as directed and meet with the psychiatrist again at the end of the study. If participants decide to continue with trazodone or wish to discontinue medication, their requests will be communicated to their family physician for any further care.

### E-CBTi intervention

Participants allocated to the psychotherapy group will receive e-CBTi during the study period. The program content involves interactive and engaging weekly therapy sessions. Participants will receive personalized feedback from a trained therapist each week. All sessions and interactions will occur through a secure online platform, OPTT. Pre-designed therapy sessions will be assigned to the patients through the platform and can be accessed at any time throughout the week. Each session consists of approximately 30 slides that take approximately 45 minutes to complete. The e-CBTi program is based on the rationale that insomnia is associated with thoughts and behaviours that cause or worsen sleep problems [14]. The e-CBTi sessions will guide participants in developing constructive and balanced strategies to help manage their sleep. The sessions aim to adjust maladaptive thinking and behaviours so that participants can use skills and strategies to think about and adapt to the events happening to them. This approach enables individuals to, allowing them to adjust their behaviour and thoughts to ones that are more balanced and realistic. Each of the structured e-CBTi sessions will focus on the concepts listed in Table 1.

**Table 1 pone.0285757.t001:** Session overview.

Session	Learning Objective / Session Description
Session 1: What is Sleep?	Provides an overview of the course and introduces the concepts of sleep, CBT, and insomnia.
Session 2: Sleep Habits	Discusses various sleep habits’ impacts on sleep. Provides stimulus control instructions, such as activities that are permitted or disallowed when in bed, daytime napping and what to do if sleep is not attained at night. Provides sleep restriction instructions, including setting specific bedtime, maintaining the same wake time, and restricting time spent in bed awake.
Session 3: Sleep Hygiene	Provides sleep hygiene education and discusses behavioural health practices, such as caffeine, alcohol, exercise, diet, smoking, and environmental factors’ impacts on sleep. Provides an overview of relaxation techniques that support sleep.
Session 4: Bedtime Worries	Introduces negative thoughts’ roles in insomnia and strategies to manage disturbing and unhelpful thoughts through the constructive worries exercise.
Session 5: Negative Thoughts	Explains the role of automatic thoughts and how they influence feelings. Provides ways to identify unhelpful thinking errors related to sleep.
Session 6: Thought Examination	Discusses elements of the thought examination process, including identifying automatic negative thoughts about sleep, evidence that supports or does not support those thoughts, alternative views of the situation, and feelings associated with the situation.
Session 7: Review	Summarizes the main concepts of CBT and the tools and skills the patient should continue to practice beyond completion of the final session.

Each session will end with a homework assignment for patients to complete, including symptom logs, self-reflective questions, and specific structured exercises such as the thought examination worksheet. Participants will submit their homework directly to the therapist through the OPTT platform. Trained therapists will review participants’ homework, sleep diary, weekly insomnia ratings, and Fitbit data and provide personalized feedback within 48 hours through OPTT. Pre-designed homework feedback templates, including session contents summary and evidence-based information, are provided to therapists as a basic structure to help standardize care, ensure feedback quality, and promote efficiency. With a particular focus on patient-centredness and self-management, therapists then personalize the feedback template to address patient-specific challenges, such as unhelpful thought patterns related to insomnia and sleep habits. Once patients receive feedback, they can ask questions, and therapists can respond to those questions under the same thread. During each session, patients and therapists can also communicate through the chat box to discuss patients’ progress and address potential challenges experienced.

### Training

All therapists will be research assistants hired by the principal investigator. They will be undergraduate and master’s students at Queen’s University with relevant psychology backgrounds and clinical experiences related to psychotherapy. They will all have undergone weekly training in CBT, psychotherapy delivery, and additional training from a licenced psychotherapist on the research team for two months before interacting with participants. During training, therapists also practice completing feedback on practice homework templates. A lead therapist on the research team will then review them and provide feedback. Following the training, all therapists will be supervised by the lead psychiatrist, an expert in e-CBTi, to provide personalized feedback and guidance for patients during the e-CBTi program. Before submitting feedback to a participant, it is reviewed by the lead psychiatrist to check for adherence to treatment content and treatment fidelity.

### Outcome evaluation

All participants are expected to wear the Fitbit sleep tracking device during the study duration and complete the Insomnia Severity Index (ISI) questionnaire and sleep diary on the OPTT platform at baseline (week 0), weekly during the study, and post-treatment (week 7–8). A tutorial for using the sleep diary on the platform will be provided to all participants. An independent researcher will collect all quantitative and qualitative measures by extrapolating recorded information through the OPTT platform.

### Primary outcome

*Insomnia Severity Index (ISI)* The primary outcome measure will be ISI [44]. ISI is a valid, reliable, and sensitive global index of self-reported insomnia symptoms that contains seven questions rated from 0 to 4 on the severity of insomnia problems, sleep satisfaction, interference of insomnia with daytime functioning; noticeability of sleep problems by others; and distress about sleep difficulties. Psychometric parameters of ISI are adequate, sensitive to change, and have been validated for online use [45].

### Secondary outcomes

Several secondary outcomes, including time in bed (TIB), sleep efficiency (SE), sleep onset latency (SOL), wake time after sleep onset (WASO), number of nocturnal awakenings (NOW), total sleep time (TST), and sleep quality (SQ) will be derived from both sleep diaries and Fitbits to assess changes in sleep outcomes from pre-treatment to post-treatment.

*Sleep Diary* A sleep diary will be used to derive secondary sleep outcomes [46]. Sleep diary has been widely used for self-reported sleep parameter assessment, and it is a reliable tool for assessing adult sleep time and quality [47]. Participants are asked to complete a web-based sleep diary on the OPTT platform for at least four days each week within thirty minutes of waking up. Four nights is chosen as the minimum required per week because a study conducted by Short et al. showed adequate reliability of four nights of sleep diary entries for assessing bedtime, sleep duration, and SOL [48]. Participants will record their bedtime, time of falling asleep, nighttime awakenings, wake-up time, and time of getting out of bed. Subjective sleep quality is rated weekly on a 1–5 scale ranging from “very poor” to “very good.”

*Fitbit* The study will also observe the data obtained from a wearable tracker (Fitbit). Participants will be provided with a Fitbit wristband to use: Fitbit Charge 2. Fitbit contains heart rate sensors and motion detectors which facilitate sleep monitoring [49]. Fitbit’s accuracy and strength in evaluating sleep are comparable to polysomnography, actigraphy, and self-reported measures, while providing less resource-intensive sleep monitoring than these instruments, which supports the reliability of using Fitbit to monitor sleep in this study [50–53]. However, despite the similarity between Fitbit and research-grade devices such as actigraphy and polysomnography performances, caution should be taken in the interpretation of the use of consumer technology [50,53]. Participants are expected to always wear the Fitbit sleep tracking device during the study duration. Data will be collected using the Fitbit application that is synced with the device and then automatically uploaded to the secure OPTT web server. Upon completion of the study, the Fitbit will be returned to the lab, and Fitbit data collected via OPTT will be used for further analyses. The combination of the subjective sleep diary, ISI questionnaire and objective Fitbit measures will be beneficial for assessing patients’ sleep outcomes and treatment effectiveness in this study.

### Additional measures

Participants will also report their baseline demographics, including their age, sex, income, ethnicity, marital status, native language, employment status, current medication usage, living arrangements, education level and medical history. Finally, quantitative behavioural measures for both groups, including the number of logins, the number of homework and questionnaires completed, and the number of sessions completed will be collected to assess patients’ engagement and adherence with the treatment. Additionally, treatment adherence in the e-CBTi group will be further explored by assessing compliance to keeping a consistent sleep schedule, avoiding naps, eliminating consuming alcohol or nicotine 2–3 hours before going to bed, getting out of bed shortly after waking and completing thought examination practices based on results from the sleep diary, Fitbit and homework for each session [54].

### Ethical considerations and data management

Patient confidentiality and data privacy will be protected throughout the study, including assessment, treatment, and data analysis, in accordance with Queen’s University ethics guidelines. All study personnel will be trained in responsible and ethical research conduct and the handling of private and confidential information through the completion of the tri-council policy statement: ethical conduct for research involving humans (TCPS 2) research ethics course prior to their involvement in the study.

All participants are expected to provide electronic or written informed consent for data to be collected before participating in the study. To ensure the safe handling of data and protect confidentiality and privacy, all research participants will be provided with a unique and randomized participant login ID and password for OPTT. All data is stored through OPTT. Data management through OPTT is in accordance with the Health Insurance Portability and Accountability Act (HIPAA), the Personal Information Protection and Electronic Documents Act (PIPEDA), and the Service Organization Control-2 (SOC-2). Moreover, data collected from OPTT is sent to secured servers and databases hosted on Amazon Web Service Canada cloud infrastructure, managed by Med stack to ensure all Canadian provincial and federal privacy and security regulations are met. OPTT will not collect identifiable personal information or IP addresses for privacy reasons. OPTT will only collect anonymized metadata to improve its service quality and provide advanced analytics data to the research team. All encrypted backups will be kept on secure Queen’s University servers. OPTT automatically encrypts all data, and no employees have direct access to patient data. Only the direct care provider, independent biostatistician, and research assistants will be able to access anonymized study records to facilitate assessment, the welfare of participants, and data analysis. Any documents with identifiable information (e.g., consent forms and personal information) will be stored locally in a locked file cabinet or online in password-protected formats. They will be stored separately from the anonymized data and may only be accessed to be integrated into data interpretation for research purposes.

### Safety considerations

Studies conducted in similar clinical populations demonstrated that low doses (25mg-100mg/day) of trazodone for managing insomnia produced mild, including daytime sleepiness and mild headaches, to no adverse effects [11]. Additionally, previous studies in similar samples have also shown that e-CBTi can be safely carried out without significant risks of unwanted effects.

Participation in this study is voluntary. Participants may withdraw from this study at any time without providing a reason, and their data will remain confidential. Participants’ withdrawal will not affect their current or future medical care, and they may continue receiving standard care procedures.

### Statistical analyses

SPSS version 25 will be used to analyze the data (e.g., analyses of missing values, baseline characteristics, the effect of the intervention, compliance rates). For all analyses, the alpha level will be set to 0.05. Initially, all data will be examined for missing, nonsensical, and outlying variables. Missing data will be treated as missing and not imputed. Participants who did not complete all seven sessions of e-CBTi or trazodone are considered dropouts. Additionally, dropout rates between groups will be compared using chi-square tests, and demographic and dependent variables will be assessed and compared between completers and participants who withdraw prematurely to estimate dropout effects. Descriptive statistics will be used to describe the sample’s baseline demographics. Group differences in baseline demographics will be analyzed using independent sample t-tests for continuous variables (e.g., age, income). Chi-square test will be used to examine group differences in categorical variables (e.g., sex, ethnicity, native language, employment status, children, current medications, education level, medication usage, living arrangements, and primary diagnosis). Data from all participants will be included in the analyses. Treatment effectiveness will be assessed using two-way ANOVA for repeated measures and multilevel regression analysis with the main effects as the group (e-CBTi vs trazodone) and time (pre-treatment to post-treatment). The group x time interaction effects for the ISI scores, sleep diary measures, and Fitbit sleep estimates will be evaluated to compare the change from pre-treatment to post-treatment between and within the groups. Descriptive statistics will be used to describe the sample and patient engagement, including the number of logins, the number of sessions completed, and the number of homework or questionnaires submitted. An independent sample t-test will be used to identify group differences regarding these behavioural variables.

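### The dropout rule counts seven sessions that only the e-CBTi arm has, so the planned between-arm dropout test has no consistent meaning

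*Protocol article*

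**What the plan says.** The dropout rule is in Statistical analyses: "Participants who did not complete all seven sessions of e-CBTi or trazodone are considered dropouts". The same section applies it at once: "dropout rates between groups will be compared using chi-square tests". Demographic and dependent variables are then to be "compared between completers and participants who withdraw prematurely to estimate dropout effects". On the analysis set the section says: "Data from all participants will be included in the analyses". Missing values are not imputed.

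The two treatments are organised differently:

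- **e-CBTi** (E-CBTi intervention): "The program content involves interactive and engaging weekly therapy sessions". Table 1 lists seven, the last being "Session 7: Review".
- **Trazodone** (Pharmaceutical intervention): a drug taken daily. The psychiatrist is seen at a first session and at the end of the study, and between these: "Additionally, a psychiatrist will follow up with the participant mid-program (week 4) via video sessions". Other contact is by telephone when the participant asks for it.

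The ISI is collected from all participants at baseline, weekly and at week 7–8 (Outcome evaluation). Under Additional measures, a set of behavioural counts is listed for both groups, among them: "the number of sessions completed will be collected to assess patients’ engagement and adherence with the treatment". Statistical analyses compares these counts between groups by t-test.

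**The concern.** One rule is written for both arms, but its unit of count exists in only one. The article does not say what completing trazodone means. It could be attending the three contacts, taking the drug to week 7, or returning the final questionnaires. Yet the rule feeds a between-arm significance test.

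The rule also merges two things that an attrition analysis should keep apart: stopping treatment and stopping the supply of outcome data. Because the ISI is collected separately from the modules, an e-CBTi participant can miss one module, return every ISI and still be a dropout. The completer comparison adds to the difficulty by switching from dropouts to people who withdraw early, which is a different group.

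At stake is a published p-value for dropout that cannot be interpreted, and a completer comparison that does not reliably describe who lacks outcome data. With no imputation, that description is what a reader needs in order to judge the ISI result.

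**Working it through.** **1. The plan's own sample size, to see whether the rule touches it.** Inputs from Sample size: f = 0.25, four measurements, correlation 0.3, alpha 0.05, two groups, N = 36. For the group × time interaction (sphericity assumed):

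- λ = f²·N·m/(1 − ρ) = 0.0625 × 36 × 4/0.7 = 12.86
- df₁ = (2 − 1)(4 − 1) = 3; df₂ = (36 − 2)(4 − 1) = 102
- power = 0.852

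The article gives no power figure. N = 36 is the smallest even N that reaches 0.85, so it reproduces if 0.85 was the target. With the anticipated 25% dropout, 36/(1 − 0.25) = 48, and 60 are planned. After 25% loss 45 remain, with power about 0.93 by the same formula. None of this depends on how dropout is defined.

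**2. The rule read literally.** Seven sessions are required in both arms. Trazodone has three scheduled contacts, so all 30 participants are dropouts. Suppose e-CBTi loses the anticipated 25%, which is 7.5 of 30, taken as 8. The table is 8 dropouts and 22 completers against 30 and 0. Expected counts are 19 and 11 in each arm:

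- χ² = 2 × (11²/19) + 2 × (11²/11) = 12.74 + 22.00 = 34.7, p < 0.0001

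The definition alone produces this, and the excess falls on trazodone.

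**3. The rule read charitably.** Take it as seven e-CBTi sessions, or the trazodone course. The second part has no definition. For illustration only, let completion of trazodone mean keeping all three contacts. Let every required contact in either arm be kept independently with the same probability q. Then dropout is 1 − q⁷ in e-CBTi and 1 − q³ in trazodone:

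| q (assumed) | e-CBTi, seven sessions | Trazodone, three contacts | Chance that the test rejects, 30 per arm |
|---|---|---|---|
| 0.90 | 52.2% | 27.1% | 51% |
| 0.93 | 39.8% | 19.6% | 40% |
| 0.96 | 24.9% | 11.5% | 26% |
| 0.98 | 13.2% | 5.9% | 16% |
| 0.99 | 6.8% | 3.0% | 10% |

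The row q = 0.96 brings the seven-session figure close to the article's 25%. Its last column, by the normal approximation at two-sided 5%, is as follows. The difference is 0.2486 − 0.1153 = 0.1333. The standard error is 0.0996 pooled and 0.0981 unpooled. Then (0.1333 − 1.96 × 0.0996)/0.0981 = −0.63, which gives 0.264.

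Adherence per contact is equal in every row, so a test that compared like with like would reject about 5% of the time. Here the excess falls on e-CBTi, the opposite of step 2.

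**4. Dropout against missing outcome.** Three sets of people are in play: those who did not complete seven sessions (the rule), those who withdraw prematurely (the completer comparison), and those without a week 7–8 ISI (missing from the final outcome). Someone who misses one module and answers everything belongs only to the first set. The article treats the first two as one and does not tie either to the third.

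**The case against.** The strongest reply is that this is loose wording in a secondary, descriptive step. All participants enter the effectiveness analyses, so the label removes nobody from the ISI comparison. The section also plans an examination of missing values, and weekly ISI records would show missingness without any dropout label. One sentence defining completion of trazodone would close the gap in the text.

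Most of this stands, and it limits the point. But a significance test on dropout is planned, and its rule cannot be applied as written to one arm. Defining completion of trazodone would make the rule usable, yet it would still set seven modules against a different kind of event and would still not mark who lacks the final ISI.

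A reader might infer more than the documents support:

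- **That the comparison is biased against e-CBTi.** The direction is not established. Step 3 points that way only if a lighter trazodone requirement is assumed, and step 2 reverses it.
- **That a completers-only efficacy analysis is distorted.** None is stated.
- **That the session rule will push e-CBTi dropout above the anticipated 25%.** That would rest on assumed, independent skip rates. The article also does not say which dropout definition its 25% used.
- **That a trazodone participant who stops early cannot be detected, or that an intake measure is wrongly absent.** The contacts at week 4 and at the end offer an opportunity to learn this, and a condensed article need not list every measure.

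**Conclusion.** The point holds as a defect in a stated rule. The chi-square comparison of dropout has no consistent meaning: it gives 30 of 30 dropouts in the trazodone arm on the literal reading, and a comparison of unlike events on the charitable one. The completers-versus-withdrawn comparison uses a different term and does not reliably identify those without outcome data.

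That the arms are not comparable follows from the documents alone. The figures of 24.9% against 11.5%, and the 26% rejection rate, do not. They assume equal and independent contact-keeping at 0.96 and three required trazodone contacts, and they serve only to show that the definition by itself can create a gap. The primary ISI analysis and the planned 60 participants are not directly affected. The change should be made, but the trial's main conclusion does not hang on it.

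**What to change.** In Statistical analyses, replace the rule with one that is identical in both arms: a participant is a study dropout if no week 7–8 ISI is available. Use that definition for both the chi-square test and the completer comparison, and drop the separate term for early withdrawal there or define it.

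Report treatment completion separately and descriptively by arm, without a between-arm test: modules completed for e-CBTi, and continuation of trazodone as recorded at the existing week 4 and end-of-study psychiatrist contacts. The article does not say what those contacts record, so this should be confirmed. For the same reason, take the count of sessions completed out of the between-group t-test.

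The cost is a wording change, filed as an amendment, as the article (Results) foresees for any modification. No new data collection is needed, because the week 7–8 ISI is already scheduled in both arms. The definition therefore also applies to the 18 participants already recruited. Sample size and treatment procedures do not change.

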**Fig 1 pone.0285757.g001:**
[figure not shown]
Standard Protocol Items: Recommendations for Interventional Trials (SPIRIT) schedule of enrollment, interventions, and assessments. Note: T = Timepoint; T1 and T2 = Baseline; T3 = Intervention; T4 = post 7-week intervention. ISI = Insomnia Severity Index; TIB = Time in Bed; SE = Sleep Efficiency; SOL = Sleep Onset Latency; WASO = Wake Time after Sleep Onset; NOW = Number of Nocturnal Awakenings; TST = Total Sleep Time; SQ = Sleep Quality. Adherence/Engagement = the number of logins; the number of homework and questionnaires completed; the number treatment sessions completed; compliance to keeping a consistent sleep schedule, avoiding naps, eliminating consuming alcohol or nicotine 2–3 hours before going to bed, getting out of bed shortly after waking and completing thought examination practices * = assessments for the e-CBTi group only.

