### Procedure

Upon completion of the initial assessment and treatment allocation, all eligible participants will be added to a secure online platform, OPTT. The OPTT system is designed by the lead author, and developed in collaboration with a team of physicians, and web developers with expertise in online CBT, neuroscience, and data. The user can operate the OPTT system on any electronic devices connected to Wi-Fi. All e-CBTi sessions and therapist-participant interactions during the study period will occur over this platform. The same set of therapists of the same orientation, training, shared environment, and supervision is used between groups to control for the potential covariates impacting the therapeutic relationship and minimize the potential of the therapist’s effects on patient outcomes. At baseline (week 0), all participants will complete a demographic survey, and clinically validated sleep questionnaires. Online questionnaires will also be completed weekly during the study period, and post-intervention (week 7–8). Participants assigned to the psychotherapy group will receive e-CBTi along with their treatment as usual (TAU) for seven weeks. TAU is defined as the standard psychiatric or pharmaceutical treatment for patients’ conditions with no restrictions apart from the use of the experimental treatment (trazodone and CBT). If TAU includes a medication that could affect sleep, the dosage must remain consistent 6 weeks prior to the study and during the study period. Participants assigned to the pharmacotherapy group will be prescribed trazodone in the first session in addition to TAU. Once post-test questionnaires are complete, participants allocated to the pharmacotherapy group will also have the opportunity to participate in the therapist-guided e-CBTi program after the study period.

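### The between-arm t-tests of sessions and homework compare work assigned to one arm only, so they reflect allocation rather than engagement

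*Protocol article*

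**What the plan says.** The Additional measures section collects "quantitative behavioural measures for both groups, including the number of logins, the number of homework and questionnaires completed, and the number of sessions completed", and presents them as indicators of engagement with, and adherence to, treatment. The Statistical analyses section first describes engagement through "the number of logins, the number of sessions completed, and the number of homework or questionnaires submitted", and then adds: "An independent sample t-test will be used to identify group differences regarding these behavioural variables".

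Other sections fix who is asked to do what during the seven weeks:

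- **Modules.** The E-CBTi intervention section states: "Participants allocated to the psychotherapy group will receive e-CBTi during the study period". The Procedure section says that "participants allocated to the pharmacotherapy group will also have the opportunity to participate in the therapist-guided e-CBTi program after the study period".
- **Homework.** It belongs to the modules: "Each session will end with a homework assignment for patients to complete" (E-CBTi intervention).
- **Trazodone contacts.** The Pharmaceutical intervention section describes a first meeting with the psychiatrist, then that "a psychiatrist will follow up with the participant mid-program (week 4) via video sessions", and a meeting at the end, with telephone calls if problems arise. It describes no modules and no homework.
- **Tasks common to both arms.** Everyone is on the platform. Everyone completes the ISI at baseline, weekly and after treatment, keeps a web diary on at least four days a week, and wears the Fitbit (Procedure, Outcome evaluation, Secondary outcomes).

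**The concern.** A between-group test of engagement is informative only if both groups could have scored on the item. Two of the listed counts fail that condition: one arm is given the modules and homework and the other is not. A t-test on these counts mainly detects the allocation.

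What is at stake is interpretation. The Introduction and Discussion argue that adherence to medication is a problem and that guided e-CBTi should improve adherence. A small p-value on sessions or homework could easily be taken as support for that argument, when it would appear even if uptake of the programme were poor.

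**Working it through.** The article gives no figure for these tests, so there is nothing to reproduce. The check takes each variable in turn.

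**Inputs from the protocol article**
- 30 per arm planned, with dropout of up to 25% (Sample size): 30 × 0.75 = 22.5, taken as 22.
- Alpha 0.05 (Statistical analyses). Sidedness is not stated; two-sided is assumed.
- Seven modules, each with homework (E-CBTi intervention).
- Diary on at least four days a week: 4 × 7 = 28 entries over seven weeks in both arms (Secondary outcomes).

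**1. Homework, and sessions if only modules count**

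The trazodone arm has mean 0 and SD 0. Let the e-CBTi arm have mean m and SD s, with n per arm. The pooled variance is s²/2, so the standard error is √(s²/2 × 2/n) = s/√n, and t = m√n/s. The test rejects when m/s exceeds the critical t (2n − 2 degrees of freedom) divided by √n:

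- n = 30: 2.002/5.477 = 0.37
- n = 22: 2.018/4.690 = 0.43

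Rejection rates were then simulated. Each e-CBTi participant's number of modules out of 7 was drawn from an assumed beta-binomial distribution (beta parameters summing to 1.5):

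| Average share of modules done | Mean of 7 | Rejection, n = 30 | Rejection, n = 22 |
|---|---|---|---|
| 5% | 0.35 | 38% | 18% |
| 10% | 0.70 | 89% | 69% |
| 20% | 1.40 | 100% | 99% |
| 30% or more | 2.10 or more | 100% | 100% |

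At 75% completion (assumed beta(3, 1), n = 30) the median t is about 17.

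**2. Sessions if psychiatrist contacts count**

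About three contacts are described (start, week 4, end) against seven modules. A trazodone participant who attends every contact scores 3. So does an e-CBTi participant who completes 3/7 = 43% of the programme. Equal counts would mean unequal adherence.

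**3. Logins**

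Both arms must log in for about 28 diary entries and for the questionnaires. The e-CBTi arm may also log in for modules, homework and feedback. The size of that excess and the SD of login counts are not given, so both are assumed. With one extra login a week (7 in total), the noncentrality is 7/(SD × √(2/n)).

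| Extra logins per week | Rejection, n = 30 (SD 20 to 8) | Rejection, n = 22 (SD 20 to 8) |
|---|---|---|
| 0 | 5% | 5% |
| 1 | 27–92% | 21–81% |
| 2 | 76–100% | 62–100% |

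The comparison is biased by unequal workload, by an amount that cannot be fixed from the article.

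**4. Questionnaires**

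The schedule is the same in both arms. With nine forms assumed, the same completion pattern (beta(3, 1)) in each arm and 30 per arm, simulated rejection is 4.8%, as it should be. If homework is added to the count, the e-CBTi arm can score up to 9 + 7 = 16 and the trazodone arm only 9, and the comparison is spoiled.

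**The case against.** Several counter-arguments deserve an answer.

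- **The protocol attributes sessions to trazodone too.** The dropout definition in Statistical analyses speaks of seven sessions under either treatment. This stands as far as it goes: the trazodone session count need not be zero. But no seven trazodone sessions are described anywhere, and the contacts that are described differ from modules in number and in kind. The test is then non-comparable rather than degenerate, which is no better. For homework there is no such reading.
- **Inapplicable items might be left missing, since missing data are not imputed.** Then there is no second group to test, and the planned t-test cannot be run on that item.
- **Logins and questionnaires are possible in both arms.** This is correct. A reader might infer that all the engagement tests are significant by construction and uninformative. The documents do not support that: logins are confounded by workload, and questionnaires counted on their own give a valid comparison.
- **Rejection still depends on engagement.** Also correct. A reader might infer significance whatever the uptake, but at 5% completion the simulated rejection is only 18–38%. The result is assured at realistic uptake, not at every uptake.
- **The Fig 1 note marks some items as "assessments for the e-CBTi group only".** The figure is not available, so it cannot be seen which rows carry the mark. It might already restrict these counts, or mark only the sleep-habit compliance items that Additional measures limits to e-CBTi. No contradiction can be claimed from it.
- **These are additional measures and the article announces no conclusion from them.** This limits the weight of the point. It does not remove it, because the variables, the groups and the test are all stated. Likewise, that none of these counts measures drug-taking is not raised as a gap: a condensed article may leave that to the full protocol.

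**Conclusion.** The point holds for sessions and homework. Their between-arm t-tests show which arm was assigned the modules, and they will be significant at any realistic uptake: the threshold is a mean of 0.37 SD with 30 per arm, or 0.43 SD with 22, when trazodone is at zero. Logins are confounded by the extra platform work asked of e-CBTi, but significance is not guaranteed. Questionnaires are comparable provided they are counted separately, which the wording of the Statistical analyses section leaves in doubt because it joins them to homework.

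The conclusion on homework rests on the stated allocation of modules. The rejection rates rest on assumed completion patterns, login SDs and extra logins, for which the article gives no values. No primary or secondary outcome is affected. The point is worth acting on because a stated analysis would mislead on a theme that the article emphasises.

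**What to change.** - Delete the between-arm t-tests on sessions, homework and logins.
- Report sessions and homework descriptively for the e-CBTi arm only, and logins descriptively by arm, noting that the platform workload differs.
- Count questionnaires separately from homework.
- Limit between-arm engagement tests to tasks asked of both arms, each as a share of what was scheduled: ISI forms returned, required diary nights entered, and nights with Fitbit data. State that these measure adherence to study assessments, not to treatment.

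The cost is a change of wording. It needs no new data, since the article already plans to collect all of these items. At the time of the article, 18 of 60 participants had been recruited, so the change could be made before analysis.
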